## Abstract

The ageing process has been associated with various geriatric issues including frailty. Without early prevention, frailty may cause multiple adverse outcomes. However, it potentially may be reversed with appropriate interventions. The aim of the study is to assess the effectiveness of nutritional education and exercise intervention to prevent frailty among the elderly. A 3-month, single-blind, two-armed, cluster randomized controlled trial of the frailty intervention program among Malaysian pre-frail elderly will be conducted. A minimum of total 60 eligible respondents from 8 clusters (flats) of Program Perumahan Rakyat (PPR) flats will be recruited and randomized to the intervention and control arm. The intervention group will receive a nutritional education and a low to moderate multi-component exercise program. To date, this is the first intervention study that specifically targets both the degree of frailty and an improvement in the outcomes of frailty using both nutritional education and exercise interventions among Malaysian pre-frail elderly. If the study is shown to be effective, there are major potential benefits to older population in terms of preventing transition to frailty. The findings from this trial will potentially provide valuable evidence and serve as a model for similar future interventions designed for elderly Malaysians in the community.

## 1. Introduction

A developing country such as Malaysia is not exempt from the fast changing demographic patterns in society and is expected to achieve the status of an ageing country by 2035 [1,2]. In line with this, the ageing process has been associated with various geriatric issues including frailty [3]. Frailty is a term commonly used by health care professionals to describe the condition of an older person who has chronic health problems, has lost functional abilities, and is likely to deteriorate further [4]. Frailty is a continuum process, and researchers commonly classify frailty into three categories (normal, pre-frail, and frail) according to the degree of deterioration [5]. Interestingly, it is not unidirectional but a dynamic and reversible process [6].

Several risk factors lead to frailty including socio-demographic status (advanced age, female, low educational, and socio-economic status), chronic disease, malnutrition, physical inactivity, cognitive impairment, poor functional status, and history of falls [2,7,8,9]. A clear relationship is also shown with adverse outcomes, such as disability/dependency, hospitalization, institutionalization, falls, poor mobility, depression, and death in community-dwelling older adults [5,10,11]. While those in an intermediate stage of frailty (pre-frail) present an increased risk of becoming frail within just three years [5].

The recent review on the global prevalence of pre-frail and frail elderly in the community ranged from 34.6% to 50.9% and 4.9% to 27.3%, respectively [12]. Asian countries recorded a higher prevalence range of pre-frailty (40% to 72%) and frailty (5% to 28%) than the global range [13,14]. Consistent with the worldwide trend, the frailty problem among Malaysian elderly has also emerged as a cause for concern [2]. In a large scale study conducted among community-dwelling elderly in an urban area in Malaysia, it was found that pre-frailty and frailty affected 61.7% and 8.9% of the older adults, respectively [15]. In addition, on the east coast of the peninsula, there are about 18.3% frail elders [16], and in Perak and Kelantan, the frailty affected 23.0% of the older adults [17].

Although the prevalence of the pre-frail elderly population is already at an alarming state, only a few interventions have focused on the pre-frail elderly population [18,19,20]. Pre-frail individuals have more than twice the risk of becoming frail compared to non-frail people [5]. However, because frailty appears to be a dynamic process and potentially reversible, implementing interventions for pre-frail elderly may prevent the development of frailty. Evidence shows that pre-frail elderly may respond better to interventions than elderly who have already moved to a frail state [21], probably due to less disability than that of the frail elderly [5]. Thus, there is potential for more intensive interventions among pre-frail elderly.

Unfortunately, research to improve frailty outcomes for frail elderly is still in its infancy, especially in Asian countries. Despite several nutritional interventions that were applied in a previous study, few convincing effects in improving frailty outcomes were apparent. Moreover, most of the studies involved supplementation and meal support, which are obviously costly [22,23,24,25] and hence run the risk of poor sustainability [3]. Even though there are limited interventions on nutrition education that have been conducted among frail elders but few studies able to report positive outcomes [26,27]. It includes the education on healthy food choices and dietary habit change [27,28].

In contrast, the evidence concerning the effectiveness of exercise intervention on the frailty outcome was undoubtedly more convincing [29,30,31,32]. In fact, exercise seems to play an essential role in any combination interventions, whereby additional intervention (e.g., nutritional intervention) can only lead to further improvement [33]. A recent systematic review suggests the importance of a combination intervention as these tend to be more effective than a single intervention [33], especially when diet and exercise are both included [33,34]. It has been shown that the characteristics of exercise programs that seem to result in better outcomes should include multicomponent training that is performed 3 days per week, with a duration of 3 months or longer and less than 60 min per session [35,36]. However, uncertainty still exists with regard to which exercise characteristics (type, frequency, and duration) are the most effective.

Evidence shows that elderly people living in rural areas have an economic disadvantage [37], which may put them at risk of being malnourished [38] and thus at high risk of being frail [39]. However, less is known about the poor elderly population living in urban areas such as the Program Perumahan Rakyat (PPR) flats in Kuala Lumpur area. In the 2000 census, Kuala Lumpur reached the status of 100 percent urban population [40]. Meanwhile, the PPR flats are low-cost public subsidized high-rise flats (5 to 18 floors) built for the resettlement of squatters and to provide housing to the economically disadvantaged individuals. According to Loh et al. [1], the PPR flats are places where the urban poor and a growing aging population reside. Thus, probably, the elderly who are living in the PPR flats are also at risk of being frail.

To the best of knowledge, there is no published frailty intervention that specifically targets both the degree of frailty and an improvement in the outcome using a combination of nutrition education and exercise interventions among Malaysian pre-frail elderly. Although a recent trial was conducted among the pre-frail elderly in Malaysia [20], the study only included single intervention and the focus was on the supplementation. Even though the supplementation given has the potential to reverse frailty and its outcomes, the efficacy remains doubtful. To address this gap, this study aims to develop, implement, and evaluate the effectiveness of a Frailty Intervention through Nutrition Education and Exercise (FINE) intervention program targeted at both improving the degree of frailty and the outcomes by using a combination of nutrition education and exercise interventions, and compare it with the general health education among Malaysian pre-frail elderly in a poor urban setting.

## 2. Materials and Methods

This study is designed and will be conducted and reported in keeping with the Consolidation Standards of Reporting (CONSORT) 2010 statement and its extension to cluster randomized trials [41].

### 2.1. Trial Design

The “FINE” project is a 3-month (12 weeks) intervention program, single-blind, two-armed cluster randomized controlled trial (cluster RCT), conducted among pre-frail elderly with a pre- and post-intervention and 3-month follow-up assessments to assess the effectiveness of the program. The trial mainly comprises nutritional education and exercise intervention among older people aged 60 years and above in the PPR flats in Kuala Lumpur. The trial is registered prospectively at ClinicalTrial.gov with registration number NCT04327544 on 30 March 2020.

### 2.2. Participants

#### 2.2.1. Ethics Approval

The clinical trial is conducted in accord with the guidelines of the Declaration of Helsinki and the guidelines of Good Clinical Practice (GCP). Written informed consent will be sought from all the study participants prior to the commencement of the study. The study already has been approved by the Ethics Committee for Research involving Human Subjects Universiti Putra Malaysia (JKEUPM) (JKEUPM-2019-335). Permission for field data collection in the PPR flats has already been attained from the Dewan Bandaraya Kuala Lumpur (DBKL), as well as the Head Officer of the PPR flats in Kuala Lumpur.

#### 2.2.2. Screening of Frailty Status

In total, there are 32 PPR flats listed under Kuala Lumpur area (DBKL, 2019). One of the PPR flats is excluded for the purpose of acceptability study as part of the development process of education materials, while the remaining 31 flats are divided into four different zones. Two zones with the highest prevalence of pre-frail elderly will be selected for the intervention study. However, due to no previous data having been recorded regarding the frailty status of the elderly, a cross-sectional study will be conducted to assess the current frailty status of the elderly. Using the one proportion formula by Daniel [42] with estimated prevalence of pre-frailty, 72.4% [14] and additional 20% subjects, the number of samples included in the screening study is 368.

Meanwhile, the minimum required cluster recruited from each zone is based on the calculation in the actual intervention study which is 4. Since there are 4 zones, in total 16 flats (cluster) will be included and randomly selected. Note that a cluster refers to one PPR building that has at least 50 residents aged 60 years and above. A proportionate sampling technique will be used for the recruitment of the respondents from each PPR to ensure that the total number of respondents will fairly represent each PPR flats. Frailty status will be assessed using Malay language standardized phenotype of frailty questionnaire [5]. The frailty phenotype evaluates five components of the frailty syndrome and allocates one point for each criterion met; respondents meeting zero criteria are defined as non-frail, whereas those meeting one or two criteria are defined as pre-frail, and those meeting three, four, or five criteria are defined as frail.

#### 2.2.3. Eligibility and Recruitment

Based on the result from the screening, two zones with the highest number of pre-frail elderly will be selected. Pre-frail people 60 years and older from the selected PPR flats will be invited to participate in this FINE program. After the invitation process, the information sheets will be distributed and explained. Those individuals that agree to participate will be requested to provide written informed consent, and subsequently, they will be further screened to identify their eligibility to participate. The inclusion and exclusion criteria are as in Table 1. Once individuals have been screened as being eligible to participate, they will be invited to attend a pre-intervention data collection (baseline assessment). The overview of the frailty intervention study flow is shown in Figure 1.

#### 2.2.4. Sample Size Calculation

The sample size for each arm was calculated by using two group mean comparison formula [25]. Both the mean and standard deviation from the study conducted by Tarazona-Santabalbina et al. [29] in Spain was used as the reference, and based on the calculation using the result for the variable of the Short Physical Performance Battery (SPPB), the sample size required for each intervention and control arm is 15 respondents.

With a hypothesized intra-cluster correlation coefficient (ICC) 0.02 [1], fixed cluster size of 4 [45], and a minimum of 15 respondents required under individual randomization, the calculated minimum required cluster size and sample size is 4 and 16 per arm, respectively. After an adjustment for the estimated response rate, a sample size of 30 respondents per arm is required to provide of 80%, with α = 0.05. In total, the respondents for both arms are 60 elderlies with approximately 8 respondents from each cluster (4 clusters for each arm).

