### 2.5. Statistical Analysis

The description of the respondents’ characteristics will be reported by group (control and intervention). Depending on the distribution of the variable of interest, the descriptive statistics of continuous data will be presented by using the mean and standard deviation and the median and the inter-quartile range. Categorical data will be presented as frequencies and percentages. For primary analysis, since there are small number of cluster, as recommended by Hayes and Moulton (2017), analysis will be conducted at cluster level instead of individual level [58]. Thus, the primary and secondary outcomes will be compared within and between groups using 2-way repeated ANOVA by general linear model. Any covariate data at baseline value will be adjusted and further test will be conducted using a repeated measure analysis of covariance (ANCOVA). If the data is not distributed normally, Kruskall–Wallis test will be used to analyze the data. Statistical significance is set at *p* < 0.05. Data will be entered and analyzed using SPSS 25.0 software.

Intention-to-treat (ITT) will be applied in the data management and analysis. All data will be processed according to their arm even if the participant did not manage to come to all the intervention sessions. It is assumed that majority of the participant in the intervention arm will receive adequate number of the intervention sessions. Action will be taken in order to prevent lower attendance from the participants such as conducting extra exercise classes for participants who could not come to a certain session. For every nutrition session, class will start with the revision on the topic that had been discussed in previous session. This can help participants who could not come to the previous nutrition session to learn the topic they missed.

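### The 80% power in section 2.2.4 omits the small-cluster correction: at the 16 analysed per arm it is derived from, a 6-df cluster-level comparison has about 65% to 71%

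*Protocol article*

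**What the plan says.** Section 2.2.4 (Sample Size Calculation) proceeds in three steps.

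- **Individual-level number.** Using SPPB results from a reference trial, "the sample size required for each intervention and control arm is 15 respondents".
- **Clustering.** With a "hypothesized intra-cluster correlation coefficient (ICC) 0.02" and 4 respondents per cluster, "the calculated minimum required cluster size and sample size is 4 and 16 per arm, respectively".
- **Response.** "After an adjustment for the estimated response rate, a sample size of 30 respondents per arm is required to provide of 80" per cent, "with α = 0.05". The response rate itself is not given. The section ends with 60 respondents in total, about 8 from each of 4 clusters per arm.

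Section 2.5 (Statistical Analysis) then says that, because there are few clusters, "analysis will be conducted at cluster level instead of individual level".

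**The concern.** A design effect allows for the correlation between residents of the same flat. It does not allow for the between-flat variance being estimated from only eight flats. Section 2.5 recognises that the number of clusters is small and chooses its unit of analysis accordingly. Section 2.2.4 sizes the trial as if that choice had no cost.

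What is at stake is the loss the trial believes it can absorb. As written, a team could fall from 30 to 16 per arm, a 47% loss, and still think it had 80% power for the effect it was sized on.

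**Working it through.** **Inputs from section 2.2.4:** 15 per arm before clustering, ICC 0.02, 4 per flat in the calculation, 4 flats per arm, 30 per arm after the response adjustment, α = 0.05, power 80%. **From section 2.5:** the cluster is the unit of primary analysis. **Assumptions:** two-sided test, equal flat sizes, flats independently randomised, no credit for baseline adjustment.

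**1. The plan's own figure**

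- Design effect: 1 + (4 − 1) × 0.02 = 1.06.
- 15 × 1.06 = 15.9, rounded up to 16 per arm. 15.9 / 4 = 3.98, rounded up to 4 flats per arm. Both match the article.
- Implied response rate: 16 / 30 = 53%.

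**2. Effect size.** The SPPB mean and SD are not printed, so the standardised difference d has to be back-solved from 15 per arm at 80% power.

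- Normal formula: d = (1.960 + 0.842) × √(2/15) = 1.023.
- t-based formula with exactly 15: d = 1.060.
- t-based formula with the 15 rounded up from just over 14: d = 1.100, the upper limit.

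With d = 1.023, 16 per arm and normal critical values, power is 80.2%. The 80% therefore reproduces with the design effect alone, and no small-cluster correction is in it.

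**3. The cluster-level comparison**

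- Degrees of freedom: 2 × 4 − 2 = 6. The critical value is 2.447 instead of 1.960.
- Variance of a flat mean, in SD² units, with m analysed per flat: v = 0.02 + 0.98/m. For m = 4, v = 0.265.
- Standard error of the difference between arms: √(2v/4) = √(2 × 0.265/4) = 0.364.
- Noncentrality at d = 1.023: 1.023 / 0.364 = 2.81. Power from the noncentral t with 6 df is 65.1%. A simulation of 200,000 trials gave 65.4%.

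**4. Over the range of d and the number analysed (ICC 0.02, 6 df)**

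| Analysed per flat | Per arm | d = 1.023 | d = 1.060 | d = 1.100 |
|---|---|---|---|---|
| 4 | 16 | 65% | 68% | 71% |
| 5.5 | 22 | 77% | 80% | 83% |
| 6 | 24 | 80% | 83% | 85% |
| 7.5 | 30 | 87% | 89% | 91% |

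80% power is reached at 24 per arm for d = 1.023 and at 22 for d = 1.060. At the upper limit d = 1.100, 21 is enough. From 30 per arm, 24 is a loss of 6/30 = 20% and 22 a loss of 8/30 = 27%.

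**5. Sensitivity to the ICC.** At ICC 0.05, 16 analysed per arm gives 62%, 65% and 68% across the three values of d.

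**The case against.** **The trial recruits 30 per arm, not 16.** The abstract speaks of at least 60 respondents being recruited and randomised, and 30 analysed per arm gives 87% or more. This stands, and it makes the shortfall conditional. A reader might infer that the trial as planned simply has 65% power; the documents do not support that. Section 2.2.4 speaks of a response rate without saying whether the loss falls before or after randomisation. If 60 are randomised and nearly all are analysed, there is no shortfall. But 30 is obtained only by inflating 16, so 16 is the number on which the 80% is claimed.

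**The effect size is inferred.** This also stands, so a range is given. No value of d consistent with 15 per arm, two-sided, brings 16 analysed per arm to 80%.

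**The planned test is not a simple t-test.** Section 2.5 names a repeated-measures ANOVA and an ANCOVA. With three assessments, the group-by-time test at cluster level would have 6 × 2 = 12 error df. Adjusting for baseline would also help. With v multiplied by (1 − r²), 5 df (one spent on the covariate) and d = 1.023, a baseline correlation of cluster means of r = 0.3 gives 66%, 0.5 gives 74% and 0.6 gives 80%. So 65% to 71% is power without that credit. It does not rescue the stated figure, because section 2.2.4 sizes a plain two-mean comparison and neither states nor uses such a correlation.

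**Two further readings should not be pressed.** The step from 4 per flat to about 8 might look like an inconsistency, but it is the response inflation itself (16/4 = 4; 30/4 = 7.5). It is also tempting to remove a degree of freedom for zone as a stratum. Section 2.2.5 allocates flats according to zone, so zone may coincide with arm and could not then be a stratum.

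**Conclusion.** The concern holds in a conditional form. The multiplication in section 2.2.4 is correct, but the 80% attached to it does not belong to the analysis fixed in section 2.5. At 16 analysed per arm, power is about 65% to 71%, a shortfall of 9 to 15 points. It recovers to 80% at about 22 to 24 per arm and to 87% or more at 30.

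These figures assume a two-sided 5% test, ICC 0.02, d between 1.02 and 1.10, equal flat sizes and no baseline adjustment. They also assume that flats are the independently randomised units. Section 2.2.5 places randomisation at zone level with two zones; if whole zones are allocated, the 6-df calculation does not apply. Finally, they concern SPPB, a secondary outcome, and say nothing about power for the primary frailty outcome.

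**What to change.** In section 2.2.4:

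- Replace the power statement with the 6-df calculation and print the SPPB mean difference and SD used. With 4 flats per arm and ICC 0.02, 80% power for that effect needs about 22 to 24 analysed per arm; the printed inputs will settle the exact number. Say that 16 analysed gives about 65% to 71%.
- State the response rate, and whether it applies before or after randomisation.
- Set a retention target of about 6 analysed per flat, that is, at most 20% to 27% loss from 30 per arm.
- State that the figures treat flats as independently randomised, and reconcile this with section 2.2.5.
- In the clause "the calculated minimum required cluster size and sample size is 4 and 16 per arm, respectively", change cluster size to number of clusters. The fixed size of 4 given earlier in the same sentence is correct and should stay.

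The cost is wording and a less favourable figure. No added recruitment is needed if 30 per arm are randomised and at least 80% are analysed.

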#### 2.2.5. Randomization and Allocation

Randomization will be conducted after the baseline assessment is completed. Randomization takes place at the zone level to reduce the risk of exposure of the control arm to the intervention effect. PPR flats with the highest prevalence of pre-frail elderly in two zones resulting from the screening will be randomized into the intervention arm and the control. Using a computer-generated random number sequence, the study statistician will allocate the PPR flats into the intervention and control group based on their zones.

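### As allocation is written, one zone goes to each arm, yet the sample size and analysis treat eight flats as the randomised units; the passages conflict and must be reconciled

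*Protocol article*

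**What the plan says.** All references are to the protocol article.

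- **Zones.** Section 2.2.2: "Two zones with the highest prevalence of pre-frail elderly will be selected for the intervention study". Section 2.2.3 also says two.
- **Flats per zone.** Section 2.2.2: "the minimum required cluster recruited from each zone is based on the calculation in the actual intervention study which is 4". The same section defines a cluster as one PPR building, not a zone.
- **Flats per arm.** Section 2.2.4: "the respondents for both arms are 60 elderlies with approximately 8 respondents from each cluster (4 clusters for each arm".
- **Unit of allocation.** Section 2.2.5: "Randomization takes place at the zone level to reduce the risk of exposure of the control arm to the intervention effect", and "the study statistician will allocate the PPR flats into the intervention and control group based on their zones".
- **Competing statement.** The Abstract says that "8 clusters (flats) of Program Perumahan Rakyat (PPR) flats will be recruited and randomized". A further sentence in section 2.2.5 also has flats in the two zones being randomised to the arms.
- **Analysis.** Section 2.5 places the primary analysis at cluster level because clusters are few, using repeated-measures ANOVA with adjustment for baseline covariates.

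**The concern.** If allocation follows zone, and there are two zones and two arms, then arm and zone are the same variable. Anything that differs between the two zones, at baseline or during the six months of intervention and follow-up, is indistinguishable from the effect of the programme. The sample size and the analysis nevertheless take the variation between flats as the error term for the comparison of arms. That variation lies within zones and says nothing about how far two zones would differ without any intervention. At stake are the stated 5% significance level, the stated 80% power and the claim that eight clusters are randomised.

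**Working it through.** **1. What the allocation text implies.** There are 2 zones × 4 flats = 8 flats, and 4 flats per arm. Allocation is by zone, so one zone (4 flats) goes to FINE and the other zone (4 flats) to control.

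**2. The plan's own sample size reproduces, but only with the flat as the unit.** The inputs from section 2.2.4 are 15 per arm under individual randomisation, ICC 0.02 and cluster size 4.

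- Design effect = 1 + (4 − 1) × 0.02 = 1.06
- 15 × 1.06 = 15.9 per arm
- 15.9 / 4 = 3.975, rounded up to 4 clusters, and 4 × 4 = 16 per arm

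This matches the stated 4 clusters and 16 respondents. No zone variance enters.

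**3. Consequences that need no assumption.**

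| Unit randomised | Error df at that level | Possible allocations | Smallest two-sided randomisation p |
|---|---|---|---|
| 2 zones, 1 per arm | 2 − 2 = 0 | 2 | 2/2 = 1.0 |
| 8 flats, unrestricted | 8 − 2 = 6 | C(8,4) = 70 | 2/70 = 0.029 |
| 8 flats, 2:2 within each zone | 8 − 3 = 5 | 6 × 6 = 36 | 2/36 = 0.056 |

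**4. Size of the error, under an assumed zone variance.** Let the outcome variance without zone be 1, the flat ICC 0.02, *m* the number analysed per flat, and *r* the zone variance as a fraction of that outcome variance. The documents give no *r*. Take *m* = 4 (the planning figure) and *m* = 60/8 = 7.5 (all recruited). The test is a two-sided t-test on 4 against 4 flat means (6 df, critical value 2.447), as the simplest form of the between-arm comparison.

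- Variance of a flat mean within a zone: v = 0.02 + 0.98/m, which is 0.265 for m = 4 and 0.1507 for m = 7.5
- Variance the test uses for the difference: 2v/4
- True variance of the difference: 2v/4 + 2r
- Type I error: P(|T₆| > 2.447 / √[(v/4 + r)/(v/4)])

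Worked example with r = 0.02 and m = 4: v/4 = 0.06625; (0.06625 + 0.02)/0.06625 = 1.302; √1.302 = 1.141; 2.447/1.141 = 2.145; P(|T₆| > 2.145) = 7.6%.

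| Assumed zone fraction r | m = 4 | m = 7.5 |
|---|---|---|
| 0 | 5.0% | 5.0% |
| 0.005 | 5.6% | 6.1% |
| 0.01 | 6.3% | 7.3% |
| 0.02 | 7.6% | 9.5% |
| 0.05 | 11% | 16% |
| 0.10 | 17% | 25% |

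If zone variance is instead counted as a share of a total variance fixed at 1, the last row becomes 18.5% and 26.2%; the other rows move by less than one point. A simulation of 200,000 trials on that second definition, with m = 7.5, gave 4.9%, 9.6% and 16.5% at r = 0, 0.02 and 0.05, in line with the formula.

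The inflation grows with *m*: more respondents per flat shrink the error term the test uses but leave 2r untouched.

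**The case against.** **The text may mean that flats are randomised.** The Abstract and one sentence of section 2.2.5 can be read so, and allocation based on zones could, taken alone, mean stratification by zone. Figure 1, which may show the allocation, is not available. This stands to the extent that the document conflicts with itself. Zone allocation is still the better reading: section 2.2.5 names the zone as the level of randomisation and gives a contamination reason that makes sense only if the arms lie in different zones. A reader might infer that zone allocation is settled beyond doubt; the competing sentences do not support that.

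**Zone variance may be small.** All flats are subsidised low-cost housing in one city, and both zones are chosen by pre-frailty. Small values are plausible, and the lower rows of the table then apply. The documents report no actual differences between zones, so any list of differing characteristics would be speculation. Equally, nothing shows that the variance is zero, and one zone per arm cannot show it.

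**Zone allocation limits contamination.** This is a legitimate aim and a deliberate choice. Contamination would ordinarily dilute an effect, whereas a zone difference can create or hide one. A reader might infer that contamination would be negligible with flats as units because each has its own hall. Section 2.3 does not say that; it places sessions in the facility area or hall of the flats.

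**Baseline adjustment.** Section 2.5 adjusts for covariates. This may narrow a baseline difference between zones, but it neither separates zone from arm in the change over time nor restores degrees of freedom.

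**Conclusion.** The point holds and should be resolved before allocation. The sections disagree on what is randomised. As zone allocation is written, each arm holds one randomised unit, and the stated alpha and power hold only if zone variance is zero. The lack of error degrees of freedom follows from the text alone. The inflation of type I error does not: it rests on an assumed zone variance, and ranges from about 5.6–6.1% at a fraction of 0.005 to about 17–25% at 0.10. At a zone fraction equal to the plan's own flat ICC of 0.02 it is 7.6–9.5%.

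A reader might go further and conclude that the trial can never attribute a difference to FINE, or that its p-value is certainly too small. The documents do not support either. Attribution is possible under an assumption of no zone effect, and the p-value is anti-conservative only if zone variance exceeds zero. The difficulty is that the design offers no way to check this.

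**What to change.** **Preferred.** In section 2.2.5, make the flat the unit of randomisation: within each selected zone, two of the four flats to each arm. In section 2.5, analyse flat-level summaries with zone as stratum (5 df). A stratified permutation test should not be the primary test, since its smallest two-sided p is 0.056.

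**Alternative.** Randomise the eight flats without restriction (6 df). A permutation test can then reach 0.029, but the zones may be unbalanced between arms.

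**If zone allocation is kept for contamination reasons.** Remove the claim that eight clusters are randomised, state that the 80% power and 5% alpha assume zero zone variance, and report a comparison of two areas without randomised inference.

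In each case, bring the Abstract and sections 2.2.4, 2.2.5 and 2.5 into agreement on the unit.

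**Cost.** A protocol amendment and a new allocation list; flats and participants stay the same. Stratifying loses one degree of freedom. At an assumed standardised difference of 1.02 (what 15 per arm implies at 80% power and two-sided 5%: 2.802 × √(2/15) = 1.02), flat ICC 0.02 and 7.5 per flat, power falls from about 87% with 6 df to about 84% with 5 df. Some contamination between flats of one zone is possible; its extent cannot be judged from the document.
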